## Abstract

**Background:**

Insulin resistance is a strong predictor of the development of type 2 diabetes mellitus. Chronic helminth infections might protect against insulin resistance via a caloric restriction state and indirectly via T-helper-2 polarization of the immune system. Therefore the elimination of helminths might remove this beneficial effect on insulin resistance.

**Methods/Design:**

To determine whether soil-transmitted helminth infections are associated with a better whole-body insulin sensitivity and whether this protection is reversible by anthelmintic treatment, a household-based cluster-randomized, double blind, placebo-controlled trial was conducted in the area of Nangapanda on Flores Island, Indonesia, an area endemic for soil-transmitted helminth infections. The trial incorporates three monthly treatment with albendazole or matching placebo for one year, whereby each treatment round consists of three consecutive days of supervised drug intake. The presence of soil-transmitted helminths will be evaluated in faeces using microscopy and/or PCR. The primary outcome of the study will be changes in insulin resistance as assessed by HOMA-IR, while the secondary outcomes will be changes in body mass index, waist circumference, fasting blood glucose, 2 h-glucose levels after oral glucose tolerance test, HbA1c, serum lipid levels, immunological parameters, and efficacy of anthelmintic treatment.

**Discussion:**

The study will provide data on the effect of helminth infections on insulin resistance. It will assess the relationship between helminth infection status and immune responses as well as metabolic parameters, allowing the establishment of a link between inflammation and whole-body metabolic homeostasis. In addition, it will give information on anthelmintic treatment efficacy and effectiveness.

**Trial registration:**

This study has been approved by the ethical committee of Faculty of Medicine Universitas Indonesia (ref: 549/H2.F1/ETIK/2013), and has been filed by the ethics committee of Leiden University Medical Center, clinical trial number: ISRCTN75636394. The study is reported in accordance with the CONSORT guidelines for cluster-randomised trials.

## Background

The number of people with diabetes mellitus is increasing worldwide [1-3]. At present, 8.3% of adults (382 million people) have diabetes mellitus [4] and Asia is a major site of this rapidly emerging epidemic [5]. In many Asian countries, including Indonesia, rapid socio-economic development has led to a shift in infrastructure, technology and introduction of Western style diets, which promotes overnutrition and sedentary lifestyles [5-8]. These changes have already led to an increasing prevalence of diabetes mellitus in Indonesia [9-12].

A strong predictor for the development of type 2 diabetes mellitus (DM2) is insulin resistance [13,14], which is caused by complex disturbances in multiple biological systems. There is now abundant evidence that inflammation [15] plays a role in the development of DM2, in addition to the more established relationship between an altered energy balance resulting from excess consumption of high-energy foods and/or decreased physical activity. In DM2 subjects, chronic low-grade inflammation is a common feature [15] which results, at least in part, from the activation of inflammatory pathways by fatty acids in multiple organs [16-18]. However, the fundamental molecular mechanisms are still incompletely understood [19].

In developing countries, infectious pressure might be one particular modifier of insulin resistance. Helminth infections, which are still endemic in many low to middle income countries, may therefore affect whole-body and tissue-specific insulin sensitivity owing to their immunomodulatory properties [20]. Previous studies have shown that helminth infections can adopt an immune evasion strategy by inducing regulatory T cells [21-26]. Hereby helminth infections may decrease systemic inflammation and subsequently the development of inflammatory diseases, including DM2 [27-30]. Studies examining the relationship between helminth infections and DM2 in both humans [31,32] and murine models [33,34] support this hypothesis. At a molecular level, mTOR, a serine/threonine protein kinase located downstream of insulin signalling, plays an essential role in immune cell energy metabolism and function [35,36]. Furthermore, it has been shown that STAT6 signalling downstream of IL-4, as well as Th2 responses induced by helminths, improve glucose metabolism and insulin signalling [33,37]. Intriguingly, in humans, immune intervention with IL-1 receptor antagonist (Anakinra) has also been shown to influence glucose metabolism [38].

Helminths are also known to reduce energy intake and thereby change the energy balance [39], which may be beneficial in terms of insulin resistance [39,40]. Helminths may therefore both directly improve insulin sensitivity via a caloric restriction state and indirectly via Th2 activation. It appears, the immune system which has evolved with helminths [41] and under conditions of low energy intake, seems to be out of balance in situations of nutritional overload and decreasing exposure to parasites [23,42]. In line with the proposed beneficial effects of helminth infections on glucose metabolism, our previous unpublished cross sectional study in Flores Island, Indonesia, has shown that subjects infected with intestinal helminths have a significantly lower insulin resistance as expressed by HOMA-IR.

Although aforementioned studies strongly suggest that there is an association between helminth infections, systemic inflammation and glucose metabolism, the causality in these relationships has not been demonstrated as yet. Therefore we have initiated a large scale cluster randomized controlled trial (RCT) with the aim to assess the effect of anthelmintic treatment on insulin resistance, the hypothesis being that reduction of worm load to undetectable levels will lead to a higher degree of insulin resistance. While study outcomes will be analysed at the individual participant level, a household cluster randomization was chosen to minimise contamination between treatment groups and therefore reinfection of treated individuals.

## Study design

### Study area

The study area is located in Nangapanda, a sub-district of the Ende District of Flores Island, Indonesia [43,44]. Nangapanda is a semi-urban coastal area with a population of approximately 22.000 people being divided over 29 villages. Our study area includes three of these villages (Ndeturea, Ndorurea 1, Ndorurea), with a total population of 3698 people, from which most of the adult population are farmers. Previous studies have shown that this area is endemic for soil-transmitted helminth (STH) infections [45]. A detailed map of the study area has been published [43].

### Trial design

The study is designed as a household-based cluster-randomized, double-blind trial with two arms. In one arm treatment is given with albendazole (single dose of 400 mg) on 3 consecutive days, while the other arm consists of matching placebo treatment (both albendazole and placebo are manufactured by PT Indofarma Pharmaceutical, Bandung, Indonesia). The treatment is provided every three months for a period of 1 year (total 4 rounds) to all household members except children below 2 years of age, while subjects aged 16 and above will undergo clinical and laboratory examination. Subjects with active treatment for diabetes mellitus, serious concomitant disease and pregnancy will be excluded.

The population was randomised by [name] and [name] using computer aided block randomization at household level, utilizing Random Allocation Software to assign treatment groups. Both study investigators and patients are blinded for treatment codes. The treatment code will be unblinded when all data needed for analysis are cleaned and entered into the database. An additional randomization was performed in a subgroup of individuals, who will undergo an oral glucose tolerance test and immunological studies in order to study glucose metabolism and immune mechanisms in more detail. For this subgroup, we aimed to select one subject per household and stratified by age group (16–36 years of age, 36–56 years of age, and >56 years of age) to ensure that sufficient numbers of all age groups are participating. Randomization was based on households.

Well trained community workers were recruited and trained to distribute the drugs. These workers were also trained to assist during clinical examination and sample collection and were involved in health promotion within the population. Community workers and research team members will directly supervise the study participants while taking the study medication, and will collect empty drug canisters at each visit to confirm compliance. Furthermore, assessment of side effects will take place during these visits and migration and death will be noted. Adverse events spontaneously reported by the patient or observed by the investigators, will be monitored throughout the study. After completion of the study, the whole study population will be treated with a single dose of albendazole (400 mg) for 3 consecutive days.

### Outcomes

As this study aims to assess the effect of anthelmintic treatment on whole-body insulin sensitivity, our primary outcome is a change in insulin resistance as assessed by HOMA-IR between both treatment arms after one year of treatment. Secondary outcomes are changes in body mass index and waist circumference, fasting blood glucose, 2 h-glucose levels after oral glucose tolerance test, HbA1c, serum lipid levels, immunological parameters, and efficacy of anthelmintic treatment.

### Sample size

Sample size is calculated according to intention to treat analysis in which we will need 1580 subjects in total. Based on our previous study [45] we assume that the average household size is 4 and that around 20% will be lost to follow up after one year. We use a significance level of 5% and a power of 80%. Correlations within households are taken into account by using the correction factor 1 + (m-1) ICC, with m being the household size and ICC the intra-class correlation. The sample size is computed for a difference in mean between the two treatment groups of 0.18 and an ICC of 0.1.

For the subgroup of individuals undergoing an oral glucose tolerance test, a sample size of 335 subjects in total is calculated assuming that around 20% will be lost to follow up after one year and using a significance level of 5% and a power of 80%. The sample size is computed for a difference in mean of 10.3 mg/dL and a standard deviation of glucose level of 30 mg/dL.

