### Data management and statistical analyses

A centrally accessible database designed in Microsoft Access is established and the data is entered by well-trained data entry personnel. Descriptive data will be summarized for continuous variables as mean +/− SD for normally distributed data and median (range) for non-normally distributed data. Categorical data will be expressed as proportions.

The effect of anthelmintic treatment on insulin resistance (HOMA-IR) as our primary outcome will be assessed using an intention to treat approach after 1 year of treatment using mixed models to account for the correlation within households, in which relevant confounders (including age, gender, BMI, village) are entered. The characterization of immune responses to helminth infections and systemic inflammation will be assessed by measuring cytokine profiles. Moreover, for these analyses multilevel modelling will be used and the use of longitudinal data will take repeated measurement into account [51]. The mediation of helminth’s effects on insulin resistance via immune responses will also be assessed.

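### On its plain reading the primary HOMA-IR comparison is an untransformed mean difference with no scale or SD given; a pre-specified log-scale model adjusted for baseline would probably be more precise, at the cost of wording only

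*Protocol article*

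**What the plan says.** Under Outcomes, the Protocol article states that "our primary outcome is a change in insulin resistance as assessed by HOMA-IR between both treatment arms after one year of treatment".

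Under Sample size, "we will need 1580 subjects in total". The inputs are 5% significance, 80% power, an average household of 4, about 20% loss to follow-up, and a design effect obtained "by using the correction factor 1 + (m-1) ICC, with m being the household size". The target is then given: "The sample size is computed for a difference in mean between the two treatment groups of 0.18 and an ICC of 0.1". No unit, scale, control mean or SD accompanies the 0.18. The oral glucose tolerance calculation in the same section does give its unit and its SD (10.3 mg/dL and 30 mg/dL).

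Under Data management and statistical analyses, "The effect of anthelmintic treatment on insulin resistance (HOMA-IR) as our primary outcome will be assessed using an intention to treat approach", by mixed models that allow for household correlation. The covariates named are age, gender, BMI and village. The list is open, but baseline HOMA-IR is not on it. Non-normal data are mentioned once, where medians and ranges are chosen for descriptive summaries. The sentence on the primary model has no matching provision.

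**The concern.** HOMA-IR is built from fasting glucose and insulin and cannot be negative. If its SD is comparable to its mean, it must have a long right tail. A linear model on that scale has skewed residuals whose spread grows with the mean, and a small share of high values supplies much of the variance. The estimate is then noisier than it need be, and an effect that acts proportionally is summarised as a fixed number of units.

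The missing scale and SD add a second difficulty: 1580 cannot be checked from the stated inputs. If the choice of scale stays open until the data have been seen by arm, two defensible analyses of the primary outcome are available and nothing says which one counts.

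**Working it through.** **Inputs from the Protocol article (Sample size):** total 1580; difference 0.18; ICC 0.1; household size 4; 20% loss; 5% significance; 80% power. **Assumed:** two-sided test and 1:1 allocation, neither of which is stated.

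**Step 1: the SD implied by 1580.**
- Design effect: 1 + (4 − 1) × 0.1 = 1.3.
- Effective number per arm: 1580 × 0.8 / 1.3 / 2 = 486.
- (1.960 + 0.842)² = 7.849.
- SD = √(486 × 0.18² / (2 × 7.849)) = 1.00.

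Forwards, SD 1.0 gives 485 per arm, 1261 after the design effect and 1577 after dropout, which matches 1580 to within rounding. Multiplying by 1.2 for dropout instead of dividing by 0.8 gives an SD of 1.02. A one-sided test gives 1.13 to 1.15. As a check on method, the glucose tolerance inputs give 134 per arm, 268 in total and 268 / 0.8 = 335, exactly as stated.

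Power at 1580 depends heavily on the SD that is not given: 88% at SD 0.9, 80% at 1.0, 72% at 1.1 and 61% at 1.25.

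**Step 2: what SD 1.0 means for a positive variable.** A normal distribution with SD 1.0 would place 16%, 7% or 2% of values below zero at means of 1.0, 1.5 or 2.0. Near-normality is therefore plausible only for means well above 2.

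**Step 3: raw against log scale.** Assume log-normal HOMA-IR, control SD 1.0, an SD proportional to the mean in each arm, a proportional effect that raises the control mean μ by 0.18, and the same design effect on both scales.
- Log-scale SD: s = √ln(1 + 1/μ²).
- Log-scale effect size: d(log) = ln((μ + 0.18)/μ) / s.
- Raw-scale effect size: d(raw) = 0.18 / √((1 + ((μ + 0.18)/μ)²) / 2).
- Power = Φ(d × √(486/2) − 1.96).

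Worked at μ = 1.0: s = √ln 2 = 0.833; d(log) = 0.1655 / 0.833 = 0.199; d(raw) = 0.18 / 1.094 = 0.165; relative efficiency (0.199/0.165)² ≈ 1.46.

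| Assumed control mean | Skewness | d(log) | d(raw) | Relative efficiency | Power, log | Power, raw |
|---|---|---|---|---|---|---|
| 1.0 | 4.0 | 0.199 | 0.165 | 1.46 | 87% | 73% |
| 1.2 | 3.1 | 0.192 | 0.167 | 1.33 | 85% | 74% |
| 1.5 | 2.3 | 0.187 | 0.170 | 1.22 | 83% | 75% |
| 2.0 | 1.6 | 0.182 | 0.172 | 1.12 | 81% | 77% |
| 2.5 | 1.3 | 0.180 | 0.174 | 1.08 | 80% | 77% |
| 3.0 | 1.0 | 0.179 | 0.175 | 1.06 | 80% | 78% |

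Raw-scale power is below 80% throughout because the SD in the arm with the higher mean rises with that mean.

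**Step 4: simulation.** 158 households of 4 per arm (632 completers, or 1580 × 0.8 / 2), log-normal data with raw SD 1.0, ICC 0.1 on the log scale, a t-test on household means, 20,000 runs.

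| Assumed control mean | Type I error, raw | Power, raw | Power, log | Share of variance in top 1% of values |
|---|---|---|---|---|
| 0.8 | 4.8% | 76% | 90% | 47% |
| 1.0 | 4.9% | 76% | 88% | 38% |
| 1.5 | 4.8% | 77% | 83% | 26% |
| 2.0 | 5.0% | 77% | 81% | 20% |

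At low means the simulated raw-scale power is slightly above the formula. An ICC of 0.1 on the log scale is smaller on the raw scale: at mean 1.0 it is (exp(0.1 × 0.693) − 1) / (exp(0.693) − 1) = 0.07.

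**The case against.** The strongest reply is that nothing in the article says HOMA-IR is modelled untransformed. A difference of 0.18 on the natural-log scale (a ratio of about 1.20) with log SD 1.0 gives the same 1580, and so does a standardised difference of 0.18. The article condenses a fuller plan, and choosing a transformation is ordinary SAP work. This stands in part. The raw scale is the plainest reading, since the target is a mean difference, the parallel glucose calculation is in natural units and no log or ratio appears anywhere. It is still a reading, and the absence of a named transformation is not in itself an error.

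The skew argument also needs a mean that the document does not give. If 0.18 and the SD refer to change from baseline, the variable is not bounded at zero and Step 2 does not apply. Both limits stand, so the results are shown as a range. The gain is small at the top of that range.

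A difference in arithmetic means is also a legitimate target, and the article does not say that the effect is proportional. The log scale is therefore a choice that has to be justified, and the raw scale cannot be called wrong.

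A reader might infer more in two ways:
- **That skew makes the primary test invalid.** With about 632 completers per arm, simulated type I error stays at 4.8–5.0%.
- **That participants with untreated diabetes will drive the result.** The exclusions under Trial design name active treatment for diabetes and do not list untreated diabetes, so very high values may be present. No number of such participants is given, so their influence cannot be sized.

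**Conclusion.** The point holds as a low-cost improvement. It does not show a flaw that invalidates the trial. On the plain reading, the plan compares untransformed means of a positive outcome, gives neither scale nor SD for its target difference, and does not name baseline HOMA-IR as a covariate although metabolic parameters are measured at baseline.

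Under log-normality, a proportional effect and an SD of 1.0 back-solved from 1580, the log scale gains about 14 points of power at a control mean of 1.0, 5 at 2.0 and 2 at 3.0. The loss is one of precision and robustness to the upper tail. These figures do not include any gain from baseline adjustment, which depends on a baseline-to-follow-up correlation that the document does not report.

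**What to change.** Before the treatment code is broken (Trial design places unblinding after data cleaning and entry):

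1. Specify log HOMA-IR at one year as the primary dependent variable in the household mixed model, with log baseline HOMA-IR as a covariate.
2. Report the treatment effect as a ratio of geometric means with its 95% CI.
3. Keep the raw-scale mean difference as a named sensitivity analysis.
4. State the scale and SD behind 0.18, and restate the planning difference as a ratio with its log-scale SD so that the sample size and the model use the same scale.

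This changes wording only and needs no new data or participants. The drawback is that the main result becomes a percentage difference instead of a difference in HOMA-IR units; the sensitivity analysis keeps the latter available. If a full protocol or SAP already fixes the scale, it is enough to cite it and align the sample size statement with it.

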## Methods

### Sample collection

At baseline all eligible subjects, aged 16 and above will be invited to visit the examination centre after an overnight fasting and to provide stool, blood and first morning urine samples. During this visit, participant’s education level and profession will be registered. After 1 year of treatment follow-up sample collection will take place as shown in Table 1.

**Table 1 Tab1:** **Study schedule of the Sugarspin project**

**Outcome**	**Baseline**	**3 monthly treatment**				**1 year follow up**
		**1st**	**2nd**	**3rd**	**4th**	
Clinical Anthropometry	**X**					**X**
Parasitological examination	**X**					**X**
Metabolic parameters	**X**					**X**
Immunological parameters	**X**					**X**
Assessment of side effects		**X**	**X**	**X**	**X**	**X**

### Clinical anthropometry assessment

Anthropometric measurements of body weight, height, waist and hip circumference are obtained using the National Heart, Lung, and Blood Institute (NHLBI) practical guidelines. To measure body weight a flat scale for mobile use (SECA Model 876, Seca Gmbh Co, Hamburg, Germany) is used, while a portable stadiometer (SECA Model 213, Seca Gmbh Co, Hamburg, Germany) is used to measure height. Waist and hip circumference are measured using ergonomic circumference measuring tape (SECA Model 201, Seca Gmbh Co, Hamburg, Germany). In addition, body fat composition is measured using a Tanita body composition analyser (TBF-300A, Tanita Corp, Tokyo, Japan). Three blood pressure measurements (left arm, sitting upright position, after resting 5 minutes) are taken from each subject, using a digital sphygmomanometer (HEM-7200, Omron Healthcare Co, Ltd, Kyoto, Japan), and calibrated using a Riester nova-presameterH-Desk model mercury sphygmomanometer (Gerhard Glufke Rudolf Riester GmbH & Co, Jungingen, Germany) and a 3MTM LittmannH Classic II S.E. Stethoscope (3 M, St. Paul, Minnesota, USA). The average of three systolic/diastolic blood pressure measurements will be used for analysis.

### Parasitological examination

To assess intestinal helminth infection, stool containers are distributed and collected by health workers. Stool samples are examined by the Kato Katz method [46] for identification and quantification of STH eggs using 2 slides for each sample. An aliquot of the fresh stool samples is frozen at −20°C in the field and subsequently at −80°C in laboratories of the Departments of Parasitology at Leiden University Medical Center, Leiden, The Netherlands and Faculty of Medicine Universitas Indonesia, Jakarta, Indonesia for DNA extraction [43]. Part of the stool sample will be saved for potential future analysis of the microbiome.

#### DNA isolation and helminth real-time PCR

DNA isolation from stool will be performed as described elsewhere [43], with some minor modifications. Real-time PCR will be performed to detect the presence of *A. duodenale*, *N. americanus* (hookworm), *A. lumbricoides* and *T. trichiura* using a method described previously [43] with some modifications.

### Blood collection

Peripheral blood is collected into EDTA and SST Vacutainers (BD, Franklin Lakes, NJ, USA). Giemsa-stained peripheral blood smear is prepared to evaluate neutrophil and eosinophil counts. In a subset of the study population, additional blood is collected in PAXgene Blood RNA Tubes (PreAnalytiX GmbH, Hombrechtikon, Switzerland) and Sodium Heparin Vacutainers (BD). Blood collected in PAXgene Blood RNA Tubes will be used to study RNA expression profiles, while blood collected in Sodium Heparin Vacutainers will be used for detailed immunological measurements as described below (section Immunological methods). All samples deriving from EDTA and SST Vacutainers (serum, plasma, cell pellet and whole blood) and all PAXgene Blood RNA Tubes are kept at −20°C at the Field Clinical Research Centre (FCRC) and will be sent on dry ice to the University’s laboratory for storage at −80°C.

